## Abstract

**Background:**

Stress urinary incontinence (SUI) is a common condition that can severely affect women’s life quality. Electroacupuncture (EA) has been proved to be an optional treatment for SUI, but the tolerance of EA becomes a factor affecting efficiency, which should not be ignored and needs to be solved urgently. The purpose of this study is to find out whether the use of alternating acupoints combination can solve this problem or not and provide an optimization of EA treatment for female SUI.

**Methods:**

This multi-center randomized controlled trial will enroll 360 patients with SUI. They will be randomly assigned to one of the three groups—sacral acupoints group (sacral group), abdominal acupoints group (abdominal group), or alternating acupoints group (alternating group)—at a 1:1:1 ratio. The patients will receive 18 sessions of EA treatment and will be followed up for 48 weeks after the treatment. The primary outcome measure of the study is the change of urine leakage at week 6. The secondary outcomes include the incontinence episode frequency (IEF), International Consultation on Incontinence Questionnaire-Short Form (ICIQ-SF), severity of SUI, patient self-evaluation of therapeutic effects, weekly usage of urine pads, ultrasonography of pelvic floor, specialty therapies for SUI, evaluation of discomfort during EA treatment, patient acceptability evaluation and adverse events related to intervention.

**Discussion:**

This trial is specifically designed to offer an optimized EA treatment for female SUI, aiming to enhance their quality of life.

**Clinical trial registration**: ClinicalTrials.gov, identifier ID:NCT05635669.

## Background and objective

Stress urinary incontinence (SUI) mainly refers to the involuntary leakage of urine when abdominal pressure increases, such as sneezing, coughing, laughing or exercise (1). According to epidemiological studies, the global prevalence of female SUI is 20%–45% (2, 3). A longitudinal study among adult women in China has found that the incidence of female SUI is 13.1 per 1,000 person-years. As the prevalence of SUI increases with age, it will still be on the rise with the aging process of China’s population (4). The clinical symptoms of SUI not only affect patients’ mental health and life quality (5), but also cause an economic burden to society (6). Thus, more attention should be paid to this public health concern.

At present, the treatment of SUI includes behavioral therapy, physiotherapy, medications, devices and surgery, among which pelvic floor muscle training (PFMT) is the most preferred treatment for patients with mild to moderate SUI (7). However, many studies have found that PFMT requires long-term adherence for at least 3 months, which is a big challenge for patients’ compliance and time (8). Therefore, the efficacy of PFMT in the treatment of SUI has not met expectations.

To solve the unmet clinical need for SUI treatment, acupuncture is gradually widely used. A previous study has demonstrated that electroacupuncture (EA) intervention can reduce the urine leakage in pad test and decrease the International Consultation on Incontinence Questionnaire-Short Form (ICIQ-SF) score, which can help patients alleviate symptoms and improve their life quality (9). However, we have found that EA tolerance may has an impact on the efficacy in SUI treatment. The curative effect in the early stage may be more obvious than that in the later due to the repeated stimulation of a certain acupoint or acupoints combination. Based on our clinical experience, the alternate use of acupoint or acupoints combination can solve this problem. Hence, this trial is designed to explore a relatively suitable application of acupoints combination and provide certain clinical evidence for the optimization of EA in treating female SUI.

## Methods

### Study design

This multi-center, randomized, controlled trial will be conducted at LongHua Hospital Shanghai University of Traditional Chinese Medicine, Obstetrics and Gynecology Hospital of Fudan University, Yueyang Hospital of Integrated Traditional Chinese and Western Medicine of Shanghai University of Traditional Chinese Medicine, and Seventh People’s Hospital. It has been approved by the Medical Ethics Committee of LongHua Hospital Shanghai University of Traditional Chinese Medicine (No. 2022LCSY084) and registered at ClinicalTrials Registry (NCT05635669). This protocol is reported based on Recommendations for Interventional Trials (SPIRIT) 2013 Checklist. Any amendment of the protocol will be recorded and reported. Women with SUI will be randomized into sacral group, abdominal group or alternating group at a 1:1:1 ratio. The flowchart of the trail is shown in Figure 1 while the schedule of enrollment, interventions, and assessment is presented in Table 1.

**Figure 1 fig1:**
[figure not shown]
Flowchart. SUI, stress urinary incontinence; IEF, incontinence episode frequency; ICIQ-SF, International Consultation on Incontinence Questionnaire-Short Form; AEs, adverse events.

**Table 1 tab1:** Schedule of recruitment, interventions and assessments.

Study period	Enrolment		Intervention						Follow-up			
Time point	Week −1	Week 0	Week 1	Week 2	Week 3	Week 4	Week 5	Week 6	Week 18	Week 30	Week 42	Week 54
Inclusion/exclusion Criteria	**X**											
Sign informed consent	**X**											
Randomization	**X**											
*Intervention*												
Sacral acupoints treatment			**X**	**X**	**X**	**X**	**X**	**X**				
Abdominal acupoints treatment			**X**	**X**	**X**	**X**	**X**	**X**				
Alternating acupoints treatment			**X**	**X**	**X**	**X**	**X**	**X**				
*Primary outcome*												
Urine leakage		**X**						**X**				
*Secondary outcomes*												
Incontinence episode frequency		**X**				**X**		**X**	**X**	**X**	**X**	**X**
ICIQ-SF		**X**				**X**		**X**	**X**	**X**	**X**	**X**
Severity of SUI		**X**				**X**		**X**	**X**	**X**	**X**	**X**
Patient self-evaluation of therapeutic effects						**X**		**X**	**X**	**X**	**X**	**X**
Weekly usage of urine pads		**X**				**X**		**X**	**X**	**X**	**X**	**X**
Ultrasonography		**X**						**X**				
Specialty therapy for SUI									**X**	**X**	**X**	**X**
Evaluation of discomfort during treatment			**X**		**X**							
Patient acceptability evaluation			**X**		**X**							
Safety evaluation			**X**	**X**	**X**	**X**	**X**	**X**				

SUI, stress urinary incontinence; ICIQ-SF, International Consultation on Incontinence Questionnaire-Short Form.

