## Outcomes

The primary outcome of the study will be the change of urine leakage between baseline and week 6 measured by the 1 h pad test. The standardized procedure of the 1 h pad test requires the patients to wear a pre-weighed pad, drink 500 mL of water within 15 min, and then complete various activities including walking, going up and down stairs, standing and sitting, picking up a coin from the floor, coughing, running, and putting their hands under running water. Afterwards, the pad will be reweighed to measure the amount of urinary leakage (13). The 1 h pad test has a high adherence rate and a specificity of 65% to 89% (14). When patients have periods or a severe cough, outcome evaluations will be postponed and rescheduled until the end of the period or the remission of the cough.

The secondary outcomes include the following ten items:

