However, this study also has some limitations. Firstly, all the 4 medical centers participating in this study are all located in the same city, which may lead to the lack of diverse regions subjects. Diverse regions such as urban and rural areas may present varying prevalence rates, causes, lifestyles, and treatment responses related to SUI. To address this concern, we will recruit participants from four large, comprehensive tertiary hospitals, with block randomization and competing enrollment, aiming to enhance the sample’s diversity. Secondly, due to all three groups being treatment groups, the acupuncturists need to perform specific maneuvers to elicit the “de qi” sensation of “swelling, soreness, numbness, and heaviness” in patients. Therefore, the study is not double-blinded, potentially hindering the exclusion of the placebo effect of acupuncture. However, it is important to note that previous studies have compared EA with placebo EA, confirming that its efficacy in addressing SUI is not attributable to a placebo effect (12). Thus, this particular concern has been mitigated. In conclusion, we hope that the results of this study will provide an optimized EA treatment for female SUI, and ultimately aiming to enhance their quality of life.

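### Table 1 randomises at Week −1 but takes the baseline pad test and patient-reported baselines at Week 0, after allocation and possibly with the group known

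*Protocol article*

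**What the plan says.** Table 1 divides enrolment into two time points before treatment starts in Week 1: "Time point Week −1 Week 0 Week 1". Eligibility, consent and randomisation ("Randomization X") are each marked once, at Week −1.

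The outcome rows have their first mark one column later, at Week 0. This applies to the primary outcome ("Urine leakage X"), to "Incontinence episode frequency X", to ICIQ-SF, to "Severity of SUI X", to "Weekly usage of urine pads X" and to ultrasonography.

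The Outcomes section defines the primary outcome as "the change of urine leakage between baseline and week 6" on the 1 h pad test, so the Week 0 value is half of the primary measurement.

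The section on randomisation, allocation concealment and blinding names assessors and statisticians as blinded. Patients and acupuncturists are not named. Sealed envelopes are opened by grouping personnel in order of hospital visits. The Discussion concedes that "the study is not double-blinded". The recruitment section requires consent before randomisation, but no section requires the baseline measurements to be complete by then.

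**The concern.** A baseline is protected by randomisation only if it is fixed before allocation can influence it. Under the printed order it is not. The pad test depends on how hard the woman coughs, runs and climbs stairs. The diary, the ICIQ-SF and the pad count are her own reports. A blinded assessor protects the weighing of the pad, but not effort or self-report.

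Two things are at stake:

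- The primary outcome is a change from this value, so a group-related difference at Week 0 can appear as a treatment effect at Week 6.
- A woman who withdraws between Week −1 and Week 0 has been randomised but has no scheduled baseline. Her change score cannot be formed without substituting another value. The Outcomes section also postpones assessments for menstruation or severe cough. If this is applied at Week 0, it lengthens the interval between allocation and baseline.

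**Working it through.** **1. Order of events, read from Table 1.**

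| Row | Week −1 | Week 0 | Next mark |
|---|---|---|---|
| Eligibility, consent, randomisation | X | – | – |
| Urine leakage (primary) | – | X | Week 6 |
| Episode frequency, ICIQ-SF, diary severity, pad use | – | X | Week 4 |
| Ultrasonography | – | X | Week 6 |

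Randomisation precedes every outcome baseline by one time point.

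**2. How a shift at Week 0 reaches the primary outcome.** Take the reduction as Week 0 minus Week 6. Suppose allocation shifts one arm's mean by b0 at Week 0 and by b6 at Week 6 for reasons unrelated to efficacy. The between-arm difference in mean reduction is then distorted by b0 − b6. If b6 = 0, the full b0 enters. If b6 = b0, it cancels. Only the part that does not persist to Week 6 does harm.

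**3. The plan's own sample size, reproduced first.** Inputs from the sample size section: mean changes 9.90, 10.30 and 11.60; SDs 2.61, 3.60 and 3.93 (sacral, abdominal, alternating); two-sided α 0.05; power 80%; 20% dropout. A three-group F-test with the largest SD, 3.93, needs 96 per group. 96 / (1 − 0.20) = 120 per group and 360 in total, as stated. The timing issue does not change this figure. It supplies the 96 evaluable women per arm used below.

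**4. Sensitivity, alternating versus sacral.**

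- SE = √((3.93² + 2.61²) / 96) = √(22.257 / 96) = 0.4815 g.
- With no true effect and an uncancelled shift b, the two-sided rejection rate is P(Z > 1.96 − b/SE) + P(Z < −1.96 − b/SE).
- b = 0.25 g: b/SE = 0.519, rejection rate about 8.1%.
- b = 0.5 g: b/SE = 1.038, rejection rate about 18.0%.
- The planned difference is 11.60 − 9.90 = 1.70 g, and 0.5 / 1.70 = 29% of it.

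**5. The same for alternating versus abdominal.** The root-mean-square SD is √((3.60² + 3.93²) / 2) = 3.77, and the planned difference is 11.60 − 10.30 = 1.30 g. Shifts of 0.25, 0.5 and 1.0 g give about 7%, 15% and 45%. The protocol names no primary pairwise contrast, so both are shown.

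All values of b are assumptions. Nothing in the protocol indicates their size or direction.

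**6. Is there a pad test before randomisation?** The diagnostic criteria require a 1 h pad test gain above 1 g, and inclusion requires mild to moderate severity on that test. Eligibility is marked at Week −1, so a value should exist by then, yet Table 1 shows no pad test in that column. Either an unmarked test was done and the later value is taken as baseline, or the Week 0 test also decides eligibility and randomisation precedes confirmed eligibility. Under either reading Table 1 needs correction.

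**The case against.** The best defence is that Table 1 works in week columns and does not give the sequence within enrolment. Both columns fall under the enrolment heading. The text does not say when the envelope is opened or when the woman is told her group, and Figure 1, which might show the order, was not available for this review. The mark may be a drafting slip. This is why the point is put conditionally. It does not remove it, because no text available here reverses the printed order.

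A second defence concerns mechanism. All three arms receive active electroacupuncture with the same number and length of sessions, so disappointment with allocation may be slight. The pad test is standardised, its assessor is blinded, and a lasting difference in effort would cancel. These arguments stand as reasons to expect a small bias. Against them, the background and Discussion state the team's hope that alternation works better, so expectations need not be equal across arms.

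Three stronger readings are tempting, and the protocol does not support them:

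- *Patients do know their group at baseline.* This is only inferred from the envelope procedure and the absence of patient blinding.
- *Any Week 0 shift passes one-for-one into the result.* That is so only if the shift is absent at Week 6.
- *The late baseline spoils a covariate adjustment.* The statistical methods section names t-tests, rank-sum tests and longitudinal models, and plans no analysis of covariance.

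**Conclusion.** The point holds as a defect in the printed schedule. Followed as written, Table 1 gives a post-randomisation baseline for the primary change score and for the patient-reported outcomes, in a trial that does not list patients as blinded. This is an avoidable exposure and should be corrected.

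The size of any bias is unknown. A reader might take the 8% and 18% as the trial's actual error rate. They are not. They rest on assumed shifts of 0.25 g and 0.5 g in one arm, no carry-over to Week 6, 96 evaluable women per arm, the planning SDs and a normal approximation. A reader might also infer that women who leave early have no pad-test value at all. The eligibility criteria suggest otherwise for the primary outcome. What such women lack is the scheduled Week 0 value, along with the diary and questionnaire baselines.

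Confidence is medium, because a drafting slip in one table cell would reduce the matter to a correction.

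**What to change.** - **Order.** Complete the Week 0 pad test, 72 h diary and questionnaires before the envelope is opened, and move the randomisation mark in Table 1 after them. If practice already follows this order, correct the mark and say so in the text. Also mark the eligibility pad test in Table 1.
- **Ultrasonography.** The Outcomes section selects thirty women within each group, so a simple rule of all baselines first does not work for this measure. Either preselect the subset in the concealed randomisation list, or scan after allocation with a blinded reader.
- **Women already randomised.** Recruitment began in January 2023. For women randomised before their Week 0 test, repeat the primary analysis as a sensitivity analysis with the pre-randomisation eligibility pad test as baseline. This requires that the value was recorded and does precede allocation.

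Cost: for the pad test, diary and questionnaires this is a change of order with no added procedure. Allocation becomes known a few days later, because the 72 h diary must be finished first. The ultrasonography rule needs either a change to the randomisation list or a blinded reader. The sample size is unaffected.

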### Patient recruitment

Eligible patients with SUI will be recruited in outpatient clinics from the four participating hospitals. And those patients will be firstly assessed for eligibility by trained personnel face-to-face following the inclusion and exclusion criteria mentioned below. Before randomization, written informed consent will be obtained from all patients. They have the right to withdraw at any time and their personal data will only be used for this study.

### Criteria for diagnosis

Patients must meet the following criteria of SUI (10):

Involuntary loss of urine with physical exertion or effort, coughing or sneezing;1 h urine pad test indicating weight gain >1 g;Absence of other symptoms of urinary frequency or urgency.

The severity of SUI is distinguished according to the 1 h urine pad test (11): normal: ≤ 1 g; mild: 1.1 g–9.9 g; moderate: 10 g–49.9 g; severe ≥50 g.

### Criteria for inclusion

Patients with mild to moderate SUI mentioned in the diagnostic criteria above;Female, aged 40–75 years;Sign the informed consent.

### Criteria for exclusion

Other types of urinary incontinence (urgent, overflow or mixed);History of urinary incontinence surgery or pelvic floor surgery;Pelvic organ prolapse ≥stage II;Symptomatic urinary tract infection;Residual urine volume >30 mL;Maximum urinary flow rate <20 mL/s.Limitation of movement (walk and/or run and/or climb stairs);Patients who have been using drugs that may affect bladder function or have been receiving SUI specialized treatment;Severe cardiovascular, cerebral, liver, kidney and hematopoietic system disease, mental disorders, diabetes, multiple system atrophy, cauda equina neuropathy and spinal cord disease;Pregnancy or lactation period;With cardiac pacemaker, EA phobia or metal allergies.

### Criteria for removal

Patients who did not complete the full course of 18 sessions over 6 weeks and did not provide a primary outcome indicator after treatment.Patients with the above exclusion criteria occurring during treatment;Voluntary patient withdrawal from study treatment;Occurrence of severe adverse events (AEs) or complications that result in stopping the trial.

### Randomization, allocation concealment and blinding

The random assignment scheme for this study was generated by the Clinical Research Center of LongHua Hospital Shanghai University of Traditional Chinese Medicine with “Proc plan” program of SAS 9.4 (SAS Institute, Cary, NC, United States). In this study, stratified randomization was adopted, with the research centers as the stratification factor. All the 4 participating hospitals will compete for enrollment. The random distribution cards sealed in opaque envelopes will be opened by the personnel for grouping according to the sequence of hospital visits so that patients can be assigned to sacral group, abdominal group or alternating group at 1:1:1 ratio. Based on the characteristics of this study, assessors for information and statisticians are blinded. Moreover, all researchers who have received training on the implementation of this research will strictly abide by the principle of departments separation.

### Interventions

All treatments will be performed after skin disinfection. As acupuncture needles are inserted, all needles will be lifted, twisted, and stabbed to activate the sensation of “de qi.” The EA stimulation will last for 30 min with a continuous wave of 50 Hz and a current intensity of 1 to 5 mA (12). In the study, sterile acupuncture needles will be used, which are from Suzhou Medical Supplies Factory Co.’s Huatuo (size 0.30 × 75 mm). Patients will receive 3 treatments per week (every other day), for a total of 18 sessions over the course of 6 weeks. The follow-up sessions are in weeks 18, 30, 42 and 54. Besides, patients are told that they cannot use specialty therapy for SUI, such as pelvic floor muscle training, electrical stimulation, biofeedback, vaginal cone and medication during the 6 weeks treatment period.

### Sacral acupoints group (sacral group)

Patients will receive EA treatment of sacral acupoints combination treatment at bilaterally Huiyang (BL35) and Zhongliao (BL33) in the prone position during the whole treatment course. In this group, paired electrodes from the EA apparatus will be attached transversely to the needle handles at bilateral BL35 and BL33. The acupoints’ locations and manipulating techniques are described in Figure 2 and Table 2.

**Figure 2 fig2:**
[figure not shown]
Locations of acupoints. BL33: Zhong Liao; BL35: Hui Yang; RN3: Zhong Ji; RN4: Guan Yuan; KI12: Da He.

**Table 2 tab2:** Locations and manipulations of acupoints.

Acupoint	Location	Manipulation
Zhong Ji (RN3)	4 cun below the navel, on the anterior midline	Needle insertion followed an angle of 30°to 45° towards perineum
Guan Yuan (RN4)	3 cun below the navel, on the anterior midline	Needle insertion followed an angle of 30°to 45° towards perineum
Da He (KI12)	4 cun below the navel, 0.5 cun lateral to the anterior midline	Needle insertion followed an angle of 30°to 45° towards perineum
Zhong Liao (BL33)	located in the third sacral foramen	Needle insertion followed an angle of 30° to 45° in an inferomedial direction
Hui Yang (BL35)	located 0.5 cun lateral to the extremity of the coccyx	Needle insertion followed an angle of 30° to 45° in a slightly superolateral direction

### Abdominal acupoints group (abdominal group)

Patients will receive EA treatment of abdominal acupoints combination at Zhongji (RN3), Guanyuan (RN4) and bilaterally Dahe (KI12) in the dorsal position during the whole treatment course. In this group, paired electrodes from the EA apparatus will be attached to the needle handles, respectively, at RN3 and left side of KI12, as well as RN4 and right side of KI12. The acupoints’ locations and manipulating techniques are described in Figure 2 and Table 2.

### Alternating acupoints group (alternating group)

Patients will receive EA treatment of sacral acupoints combination and abdominal acupoints combination alternately. (For example, A for the first time, B for the second time, A for the third time, and so on). The application of EA is the same as that of sacral group and abdominal group.

## Outcomes

The primary outcome of the study will be the change of urine leakage between baseline and week 6 measured by the 1 h pad test. The standardized procedure of the 1 h pad test requires the patients to wear a pre-weighed pad, drink 500 mL of water within 15 min, and then complete various activities including walking, going up and down stairs, standing and sitting, picking up a coin from the floor, coughing, running, and putting their hands under running water. Afterwards, the pad will be reweighed to measure the amount of urinary leakage (13). The 1 h pad test has a high adherence rate and a specificity of 65% to 89% (14). When patients have periods or a severe cough, outcome evaluations will be postponed and rescheduled until the end of the period or the remission of the cough.

The secondary outcomes include the following ten items:

The change of mean incontinence episode frequency (IEF) in 72 h.The change of International Consultation on Incontinence Questionnaire-Short Form (ICIQ-SF). It is a brief instrument used to assess the IEF or the volume of incontinence, as well as the impact of life quality during the previous four weeks. We will utilize the Chinese version due to its characteristics of a patient-centered life quality assessment tool. This version is easy to understand and has good internal consistency and reliability (15). Scores range from 0 to 21, with higher numbers denoting more severity (16).Severity of SUI. It is recorded by patients in 72 h bladder diaries. The following will be the levels of leakage: mild (a few drops), moderate (leak that soaked through underpants), and severe (leak that soaked through outerwear). If patients wear urinal pads, the severity of SUI will be assessed accordingly. Mild (few drops of leakage), moderate (soaked urine pads in patches by several leakages), and severe (soaked urine pads in patches by one leakage). The most extreme level of urine leakage will be used as the severity of SUI for analysis (12).Patient self-evaluation of therapeutic effects. It will be observed with 0 to 3 indicating “no help,” “small help,” “medium help” and “great help” respectively (12).Weekly usage of urine pads. Calculation methods at different time points will be as follows: weekly consumption of urine pads during weeks 1–6 equals the total of urine pads consumed during weeks 1–6 divided by 6; while the weekly consumption of urine pads during weeks 7–18 equals the total of urine pads consumed during weeks 7–18 divided by 12 (12).The change of ultrasonography of pelvic floor from baseline to week 6. The indicators include bladder neck mobility, urethral rotation angle, rectovesical angle, lowest point of bladder, urethral funnel formation, the type of bladder bulging both at rest and during a Valsalva maneuver by ultrasonography (17). Thirty patients in each group will be randomly selected for this examination.Specialty therapy for SUI. Application of specialty therapy for SUI will be observed at follow-up (weeks 18, 30, 42, 54). The number of patients using the specialty therapy and the frequency of treatment will be recorded.Correlation analysis. The correlation between 1 h pad test and severity of SUI in week 6. The correlation between IEF in 72 h and severity of SUI in weeks 18, 30, 42, and 54.Evaluation of discomfort during EA treatment: Visual analog scale (VAS) will be used to evaluate the degrees of discomfort during treatment. The scale ranges from 0 to 10 cm, with 0 cm indicating no discomfort and 10 cm indicating severe discomfort. The average value of the first and ninth acupuncture treatments will be taken within 5 min after the end of the treatments. If the VAS value is missing in one of the cases, another will be taken as the result.Patient acceptability evaluation: 0 = very difficult to accept, 1 = slightly difficult to accept, 2 = acceptable, 3 = easy to accept, 4 = very easy to accept. The average value of the first and ninth acupuncture treatments will be taken within 5 min after the end of the two treatments. If the VAS value is missing in one of the cases, another will be taken as the result.

The time point of measures 1.2.3.4.5 will be in weeks 4, 6, 18, 30, 42, and 54.

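### Discomfort and acceptability are rated only after sessions 1 and 9, so each alternating-arm patient is rated twice after her starting acupoint set and never directly after the other set

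*Protocol article*

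**What the plan says.** The protocol article (Interventions) sets the schedule: "Patients will receive 3 treatments per week (every other day), for a total of 18 sessions over the course of 6 weeks". In the alternating arm, "Patients will receive EA treatment of sacral acupoints combination and abdominal acupoints combination alternately", and the order is illustrated as "For example, A for the first time, B for the second time, A for the third time, and so on". The text does not say which set is A, or whether every patient starts with the same one.

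Under Outcomes, the discomfort VAS (0 to 10 cm) is defined by "The average value of the first and ninth acupuncture treatments will be taken within 5 min after the end of the treatments". The acceptability item, scored 0 to 4, has nearly the same sentence: "The average value of the first and ninth acupuncture treatments will be taken within 5 min after the end of the two treatments". Both items carry the same rule for an absent rating: "If the VAS value is missing in one of the cases, another will be taken as the result". Table 1 marks both outcomes in weeks 1 and 3 only. No other rating time is given, and nothing adapts the timing to the alternating arm.

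The two sets are delivered differently. The sacral arm is needled at "bilaterally Huiyang (BL35) and Zhongliao (BL33) in the prone position during the whole treatment course". The abdominal arm is needled at two midline points and "bilaterally Dahe (KI12) in the dorsal position during the whole treatment course".

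**The concern.** The alternation repeats every two sessions, and the two rated sessions are eight apart. Both ratings therefore fall at the same place in the cycle. In the two fixed-site arms this is harmless, because every session uses the same set. In the alternating arm, the average of the two ratings describes one set but would be analysed as the score of the regimen.

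The sets differ in body site and patient position, so equal discomfort cannot be presumed. The alternating arm is the one whose advantages the trial sets out to confirm (Discussion), so its tolerability profile will be read closely. No later analysis can recover ratings of the other set that were never collected.

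**Working it through.** **Schedule.** 3 sessions a week × 6 weeks = 18 sessions, which reproduces the protocol's figure. Session k falls in week ⌈k/3⌉: session 1 in week 1 and session 9 in week 3, as Table 1 marks.

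**Set at each rated session.** Odd sessions use the starting set and even sessions the other.

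- Starting with A: ABABABABABABABABAB. Session 1 = A, session 9 = A.
- Starting with B: BABABABABABABABABA. Session 1 = B, session 9 = B.

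Either way a patient has 9 sessions of each set. She is rated after 2 of the 9 with her starting set and 0 of the 9 with the other.

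**Effect on the arm mean (VAS).** Let s and b be the mean ratings of the sacral and abdominal sets, d = s − b, and p the share of alternating-arm patients who start with the sacral set. Assume for now that a set is rated alike in the alternating arm and in its fixed-site arm at the same session.

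- Regimen mean: (9s + 9b)/18 = (s + b)/2
- Measured mean: ps + (1 − p)b
- Bias: ps + (1 − p)b − (s + b)/2 = (p − ½)d

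The true contrasts are −d/2 against the sacral arm and +d/2 against the abdominal arm. The measured ones are:

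| p | Bias | Contrast with sacral arm | Contrast with abdominal arm |
|---|---|---|---|
| 1 | +d/2 | 0 | d |
| 0.75 | +d/4 | −d/4 | 0.75d |
| 0.5 | 0 | −d/2 | d/2 |
| 0 | −d/2 | −d | 0 |

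**Size.** The document gives no discomfort figure for either set, so d is an assumption. With a common start, d = 0.5 cm gives a bias of 0.25 cm and d = 2 cm gives 1 cm. With similarly tolerated sets it is negligible.

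**Limit of the assumption.** At session 1 with a common start, the alternating arm and the matching fixed arm have had the same treatment. At session 9 the alternating-arm patient has had five sessions of her starting set (1, 3, 5, 7, 9) and four of the other. The fixed-arm patient has had nine of one set. Any effect of that history enters the session 9 rating, which is half of the average.

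**Check of the remedy.** Session 8 falls in week ⌈8/3⌉ = 3. Sessions 1 and 8 give A and B, or B and A, so each patient's expected average is (s + b)/2 whatever p is.

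**The case against.** A reader might infer that the alternating arm as a whole rates only one set, so that its difference from one fixed arm is zero by construction. The document does not support that. The order is given only as an example, and no common starting set is stated. With a 50:50 mix of starting sets this mechanism leaves no bias in the arm mean. Even with a common start, the different exposure history at session 9 means the contrast shrinks towards zero but is not forced to zero. The trial's own rationale is adaptation to repeated stimulation, so that history cannot be dismissed.

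A reader might also infer that both outcomes fail equally. The VAS is tied to discomfort during the treatment. The acceptability item does not say whether the patient judges that session or the course so far. By session 9 she knows both sets and may well be judging the regimen. At session 1 she cannot be.

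The matter is confined to two of ten secondary items, and adverse events, including other discomforts, are recorded throughout weeks 1 to 6. So tolerability of the unrated set is partly captured elsewhere.

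These points limit the size and reach of the problem. They do not remove the within-patient defect, which holds for either starting order. Nor is this a detail left to an analysis plan: the rated sessions are stated outright.

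**Conclusion.** The point stands at patient level. Under session-by-session alternation, no alternating-arm patient is rated directly after her second set, so her discomfort average is not a score of the regimen. For acceptability the defect is certain at session 1 and arguable at session 9.

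At arm level the bias is conditional. It is about d/2 with a common starting set, where the contrast with the same-set arm shrinks towards 0 and the contrast with the other arm is about d instead of d/2. It is smaller with a mixed start and nil at 50:50. The 0.25 to 1 cm range rests on the assumed d.

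The pad-test primary outcome and the sample size are untouched. This should be fixed for two secondary outcomes; it does not threaten the trial's main conclusion.

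**What to change.** - In all three arms, take both ratings after one odd and one even session, for example sessions 1 and 8. This keeps the week 1 and week 3 marks of Table 1 and adds no visit or rating.
- Record on the case report form which set was used at each rated session.
- Replace the single-rating rule in the alternating arm. With one odd and one even session, a lone rating would again let one set stand for the regimen. Either treat the average as missing, or model the session-level ratings with set as a factor. The rule under acceptability should also refer to that scale, since it now names the VAS.
- For patients already rated at sessions 1 and 9, report alternating-arm values as scores of the set actually used, not of the regimen.

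The cost is a short amendment and a form change, plus mixed rating times between patients enrolled before and after it, which the analysis must handle. Recruitment began in January 2023 and the trial period ends in March 2025. Counting back 54 weeks, a patient with full follow-up must have begun by about mid-March 2024. If enrolment has closed, only the recording of sets (from treatment records), the missing-rating rule and the reporting rule can still be applied.
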